### Secondary hypotheses

1. It is hypothesised that participants in the intervention group will report significant reductions in social anxiety severity between baseline (T1) and post-intervention (T2) assessments.

2. It is hypothesised that among participants who met Mini criteria for SAD at baseline (T1), that significantly more participants in the intervention group will no longer meet criteria for SAD at the three month follow-up (T3) relative to the control group.

3. It is hypothesised that participants in the intervention group will report significantly fewer symptoms of anxiety and depression following treatment of social anxiety than participants in the control group.

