#### Baseline assessment (T1)

Baseline assessments are administered using a standardised protocol. All researchers received prior training on the instruments used in the assessment prior to conducting interviews. In addition, new research officers conducted a number of practice assessments with a clinical psychologist at OHV prior to working with clients. The first assessment conducted by new research officers was also co-administered by a clinical psychologist at OHV, in order to ensure adherence to the assessment protocol, and to assess interrater agreement. Research officers are fully briefed as to the requirements associated with duty of care, and are made aware of the safety protocols outlined by OHV. Given the time commitment associated with the baseline (approximately 1 ½ - 2 hours) participants are reimbursed with a $25 retail voucher. For a list of measures used in the baseline assessment, see Table 1.

**Table 1 T1:** Measures administered at each assessment

**Measure**	**Baseline (T1)**	**Post intervention (T2)**	**Follow-up (T3)**
Demographic questions	✓	-	✓
TLFB	✓	-	✓
MINI	✓	-	✓^a^
ASSIST	✓	-	✓
LSAS	✓	✓	✓
BAI	✓	✓	✓
BDI	✓	✓	✓
CMR	✓	✓	-
CSQ-8	-	✓^b^	-

*Note.* TLFB = Timeline Follow-back Method, MINI = Mini International Neuropsychiatric Interview, ASSIST = Alcohol, Smoking and Substances Involvement Screening Test, LSAS = Liebowitz Social Anxiety Scale, BAI = Beck Anxiety Inventory, BDI = Beck Depression Inventory-II, CMR = Circumstances, Motivation and Readiness for Treatment Scale, CSQ-8 = Client Satisfaction Questionnaire-8.

^a^only modules F, I and J are administered. ^b^only administered to intervention clients.

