## Data analysis

1. Differences between the intervention and control groups in categorical DVs (entry to the TC, TC stays of at least 30 days, 45 days and 90 days) will be analysed using binary logistic regression chi-square analysis.

2. Differences between the intervention and control groups in time spent at the TC will be analysed using Analysis of Variance, and Cox Proportionate Hazard Models.

3. Differences between the intervention and control groups in psychological outcomes over time (i.e., LSAS, BDI and BAI) will be explored using linear mixed modelling. In order to select the appropriate correlation structure for each of these DVs, linear models will initially be fitted using one of three possible correlation structures; compound symmetry (non-zero uniform correlations and uniform variance between time points), first order auto-regressive (observations closers in time are more highly correlated than observations further apart), and scaled identity (uniform variance across time with zero correlations between time points). The best fitting model for each outcome variable will be decided by selecting top fitting models based on Akaike’s Information Criterion (AIC).

4. Differences between the intervention and control groups in number of participants who no longer meet Mini criteria for SAD at the three month follow-up will be assessed using a 2 (intervention vs. control group) × 2 (SAD vs. no SAD) chi-square analysis. This analysis will only be conducted with participants who met Mini criteria for SAD at the baseline assessment (T1).

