### Power analysis

Power analysis indicates that an overall sample size of 121 is required to detect a medium effect size (approx .70) at the .05 alpha level using linear techniques (power = .80). On the basis of a previous study conducted at Odyssey House Victoria [70] it is expected that approximately 21% will be lost to follow up hence the target of the current study will be a sample of 146.

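### The unadjusted 2×2 chi-square for SAD remission leaves baseline severity unused and, on observed cases, is exposed to remission-related loss that differs by arm; a baseline-adjusted logistic regression is a better main test

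*Protocol article*

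**What the plan says.** Secondary hypothesis 2 in the protocol article states that, among those with MINI SAD at T1, "significantly more participants in the intervention group will no longer meet criteria for SAD at the three month follow-up (T3) relative to the control group". Data analysis, item 4 fixes the test: the difference "will be assessed using a 2 (intervention vs. control group) × 2 (SAD vs. no SAD) chi-square analysis". It defines the analysis set by baseline status alone: "This analysis will only be conducted with participants who met Mini criteria for SAD at the baseline assessment (T1". The article gives no rule for a participant whose T3 diagnosis is unknown.

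Table 1 schedules the MINI at T1 and T3 and not at T2. At T3 "only modules F, I and J are administered", and the Measures section confirms that the social anxiety section is among them. LSAS, BAI and BDI are taken at all three time points. T3 falls three months after entry to the therapeutic community (TC), or six months after baseline for those who do not enter, so non-entrants are not missing by design.

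Under Power analysis, "it is expected that approximately 21% will be lost to follow up". That figure is for the whole sample. It is not split by arm or by baseline SAD status. Item 3 of the same section analyses LSAS, BDI and BAI by linear mixed models.

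**The concern.** A participant with no T3 interview has no post-baseline diagnosis, because the MINI is not repeated in between. A 2×2 table of arm by diagnosis has no covariates. It therefore cannot use baseline LSAS, which is measured in everyone and should predict remission, nor the T2 scores of those who are later lost.

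Only one arm receives sessions. If, say, participants who remain highly anxious after the programme stopped attending, with no matching pattern among controls, the observed remission rate would rise in the intervention arm alone, and an observed-case chi-square would credit that to treatment. The mixed models of item 3 can use partial records, so the two analyses of social anxiety would treat the same lost participants differently. The test also works on a subset, those with baseline SAD, so each lost diagnosis costs precision that covariates could partly restore.

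**Working it through.** **Inputs.** From the Power analysis section: 121 required, 21% loss, target 146. The plan's own figure reproduces as 121 × 1.21 = 146.4. (Dividing instead gives 121 / 0.79 = 153.2; that is a separate matter and is not used here.) The baseline SAD share is not given for this trial. I assume 56%, the upper comorbidity figure for treatment seekers in the Background, with a range of 30% to 100%. I also assume that the 21% applies equally to this subset and to T3 MINIs. Remission rates are assumptions.

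**1. How many are scored.** Scored = 146 × share × 0.79.

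| Baseline SAD share | Baseline SAD | Scored at T3 |
|---|---|---|
| 30% | 44 | 35 |
| 56% | 82 | 65 |
| 80% | 117 | 92 |
| 100% | 146 | 115 |

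**2. Precision at 56%.** With 35% remission in both arms, SE = √(2 × 0.35 × 0.65 / n per arm). With 41 per arm this is 0.105; with 32.5 per arm it is 0.118. For 30% v 60% remission, power with 41 per arm is .79 if all are scored and .69 if 79% are.

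**3. When bias arises.** Take no true effect and remission p = 40% in both arms. Let a be the fraction of remitters lost and b the fraction of the others lost. Observed remission = p(1 − a) / [p(1 − a) + (1 − p)(1 − b)].

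- Loss of 32% v 10%, unrelated to remission: 40% v 40%. Difference 0, type I error .05.
- 21% loss in both arms with the same dependence (a = 10%, b = 28.3%): 0.36 / 0.79 = 45.6% in each. Difference 0, type I error .05.
- 21% in each arm, that dependence in the intervention arm only: 45.6% v 40%, so +5.6 points. Type I error is about .07 with 82 baseline SAD cases and .09 with 146.
- 32% v 10%, dependent in the intervention arm only (a = 12.5%, b = 45%): 0.35 / 0.68 = 51.5% v 40%, so +11.5 points. Type I error is about .15 to .23.

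So neither unequal loss alone nor an equal dependence on outcome misleads the test under no effect. A dependence that differs by arm does.

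**4. Loss driven by measured scores.** This simulation assumes a T1–T2 LSAS correlation of 0.7, latent remission correlated 0.6 with T2 LSAS, 35% true remission in both arms, 79% attendance per arm, and loss tied to T2 LSAS in the intervention arm only.

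| Log-odds of loss per SD | Observed-case difference | Adjusted for baseline LSAS |
|---|---|---|
| 0.7 | +2.9 points | +1.5 points |
| 1.0 | +3.7 points | +1.8 points |

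Against the SE of 0.118, the unadjusted bias is 0.029 / 0.118 = 0.25 to 0.037 / 0.118 = 0.31 standard errors. A shift of 0.31 SE takes two-sided type I error from .05 to about Φ(−1.65) + Φ(−2.27) = .049 + .012 = .06.

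In simulated trials with 64 scored, adjusting for baseline LSAS raised power from .74 to .78, with type I error near .05.

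Multiple imputation from T1 and T2 scores brought the mean difference to 0.000 at log-odds 1.0 and −0.004 at 0.7. At log-odds 1.0 the SD was 0.107, against 0.113 for observed cases. That is a best case, because every simulated participant had a T2 score.

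**The case against.** The strongest reply is that the article names a test, not a missing-data rule. Its analysis set is everyone with MINI SAD at T1. A chi-square can be run with the lost counted as still having SAD, or on imputed tables. Such a rule is commonly left to a full protocol or analysis plan, which is not shown. This stands. A reader might infer that item 4 commits the trial to dropping 21% of this subset and is therefore biased towards the intervention. The documents support neither step: complete-case analysis is not stated, the 21% is for the whole sample, and nothing predicts remission-related loss that differs by arm.

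The trial's own rationale makes such a difference conceivable. It holds that social anxiety impedes entry and retention, and that the intervention will change both. If residents are easier to interview, T3 attendance could then depend on anxiety and on arm. That residents are easier to interview is an inference, not something the article says.

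Three further points stand in part:

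- An unadjusted chi-square is a valid comparison of randomised groups.
- The contrast with item 3 is weaker than it looks. One of its candidate structures, scaled identity, has zero correlation between time points and would borrow nothing from earlier scores. Item 3 also covers LSAS at T3, so social anxiety at follow-up does not rest on item 4 alone.
- Imputation may recover less than the simulation shows. In the intervention arm T2 follows session four, so participants who leave the programme early may have no T2 score.

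None of this makes the chi-square the better choice. Baseline LSAS is collected, the stated test leaves it unused, and adjustment costs almost nothing.

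**Conclusion.** The point holds as an improvement to the stated method for one secondary hypothesis, not as a demonstrated bias. On observed cases, item 4's test discards baseline severity and is exposed to remission-related loss that differs by arm. Under the stated assumptions (82 with baseline SAD, 35% remission and 21% loss in both arms, loss tied to T2 LSAS in one arm only), the false benefit is about 3 to 4 points, roughly 0.3 SE. Adjusting for baseline LSAS about halves it and adds a little power. If loss depends directly on remission in one arm, the bias can be larger: 5.6 points in the 21% example. Baseline adjustment removes only the part of the selection that baseline LSAS carries. If loss is unrelated to remission, or related in the same way in both arms with no true effect, there is no bias and the gain is precision alone. The baseline SAD share, remission rates and loss patterns are all assumptions, since the documents give none of them for this subset.

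**What to change.** In Data analysis, item 4, replace the chi-square as the main test by a logistic regression of T3 MINI SAD status on arm and baseline LSAS. The analysis set is all randomised participants with MINI SAD at T1. Report the standardised risk difference, averaged over that set.

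Add two sensitivity analyses:

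- Multiple imputation of missing T3 diagnoses, by arm, from the T1 scores, any available T2 LSAS, BAI and BDI scores, and TC entry.
- An analysis that counts all lost participants as still having SAD.

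Keep the observed-case chi-square as a supporting result. If an unshown plan already handles missing T3 diagnoses, a sentence pointing to it settles that part, and the choice of main test remains.

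The cost is some wording and a little more analysis, with no new data, visits or participants. The downside is dependence on a model, and imputation recovers less where T2 is also missing.

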### Power analysis

Power analysis indicates that an overall sample size of 121 is required to detect a medium effect size (approx .70) at the .05 alpha level using linear techniques (power = .80). On the basis of a previous study conducted at Odyssey House Victoria [70] it is expected that approximately 21% will be lost to follow up hence the target of the current study will be a sample of 146.

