#### Randomisation

Following the baseline interview, an independent researcher randomises participants to either the intervention or control group. A permuted block randomisation procedure is utilised (e.g., Altman et al., 2001) whereby participants are allocated to the intervention or control group through the use of a randomly generated number. The permuted blocks are organised in groups of four (e.g., AABB, ABAB, BBAA) the details of which are not known by investigators involved with the administration of the trial. A random number sequence is generated which indicates the block of four conditions to be utilised for the following four cases. The use of the permuted block randomisation process ensures that intervention group numbers are balanced at the end of each block and is thus the recommended process in studies with smaller samples (i.e., n < 100).

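### The power statement pairs figures that do not fit: read as a standardised mean difference, .70 needs about 68 participants in total, while 121 gives 80% power at about 0.51

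*Protocol article*

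**What the plan says.** The Power analysis section is the only sample-size justification in the article. It states that "an overall sample size of 121 is required to detect a medium effect size (approx .70) at the .05 alpha level", with power .80, "using linear techniques". The total of 121 is then raised to a target of 146 for an expected loss of about 21%; that step is a separate matter and is not examined here.

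The Randomisation section describes two arms balanced in blocks: "The permuted blocks are organised in groups of four (e.g., AABB, ABAB, BBAA". Allocation is therefore 1:1.

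The Data analysis section assigns linear mixed models to the psychological scales (LSAS, BDI, BAI). It assigns logistic regression or chi-square to TC entry and to stays of at least 30, 45 and 90 days. Both primary hypotheses, entry and a stay of at least three months, are binary.

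**The concern.** Alpha, power, effect, total sample size and allocation are all printed, so the sentence can be checked. Two things look wrong. A standardised difference of .70 is large enough that a two-arm trial should need far fewer than 121 participants. And .70 is called medium, a label that by convention belongs to a standardised difference near 0.5.

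At stake is what the trial was sized to detect. If .70 is the planning effect, 121 is well above the stated requirement. If 121 is the planning figure, the printed detectable effect is too large by about 0.19 SD, and a reader could wrongly suppose that differences between about 0.51 and .70 SD were beyond the trial's reach. The sentence does not let the reader tell which applies.

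**Working it through.** **Inputs.** Alpha .05, power .80, effect .70 and total 121 come from Power analysis; 1:1 allocation comes from Randomisation. Two points are assumed because the article does not state them: the test is two-sided, and .70 is a standardised mean difference d.

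**Step 1: try to reproduce 121.** Normal approximation: n per arm = 2(z₀.₉₇₅ + z₀.₈₀)² / d² = 2(1.960 + 0.842)² / 0.70² = 2 × 7.849 / 0.49 = 32.04, so 33 per arm, 66 in total. The noncentral t calculation gives 33.02, so 34 per arm, **68 in total**. The stated 121 is not reproduced. The gap is 121 − 68 = 53, or 53/68 = 78%.

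**Step 2: the effect that 121 detects.** d = 2(1.960 + 0.842) / √121 = 5.603 / 11 = 0.509. The t-based value is 0.514. So 121 has 80% power at **d of about 0.51**, and 0.70 − 0.51 = 0.19.

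**Step 3: power of 121 at .70.** With 60.5 per arm, d√(n/2) = 0.70 × √30.25 = 0.70 × 5.5 = 3.85, and Φ(3.85 − 1.96) = Φ(1.89) = 0.971. The t-based value is 0.968, so power is **about 97%**, not 80%.

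**Step 4: the conventional medium effect.** d = 0.50 needs 128 in total (t) or 126 (normal), and 121 gives 78% power there. So 121 is close to a d = 0.50 calculation but is not exactly one.

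**Step 5: other readings of the stated inputs.**

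| Reading | Result |
|---|---|
| d = .70, one-sided | 52 |
| d = .70, power .90 | 88 |
| d = .70, power .95 | 110 |
| d = .70, alpha .025 | 82 |
| correlation r = .70 | 14 |
| chi-square effect w = .70 | 17 |
| difference in proportions h = .70 | 66 |
| hazard ratio .70 | 247 to 253 events |

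None gives 121.

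**Step 6: readings that come near 121 with added assumptions.**

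- Group difference in change from baseline, effect scaled to the SD at one time point, so that the variance of change is 2(1 − ρ): ρ = .05 gives 124, ρ = .08 about 120, ρ = .10 gives 118. At ρ = .50 it is 68 again.
- Omnibus regression test with f² = d²/4 = 0.1225: six predictors give 118, seven give 125. One predictor gives 67.
- Reading .70 as a proportion, against 45% in the other arm: 122. The sentence calls .70 an effect size, and no control-arm rate is given as a planning input.

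None of these added assumptions is in the article.

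**The case against.** The strongest reply is that the article names no metric, no test, no sidedness, no number of predictors and no within-person correlation. The mismatch then depends on a reading that the reader supplies. The planned model for the scales is a linear mixed model over time, not a single comparison of means, and some readings do give totals well above 68. An article may also condense a fuller calculation.

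Part of this stands. The figure 68 is conditional on .70 being a standardised difference in a two-group comparison, and it would be too strong to say that no reading leads to 121. But the readings that come close need either a near-zero correlation between repeated scores on the same scale, which is implausible for LSAS, BDI or BAI, or six or seven predictors tested together, which does not address a two-arm contrast. Adjusting for baseline multiplies the variance by 1 − ρ², which is at most 1, so it moves the requirement below 68 rather than towards 121. Condensation explains missing detail; it does not make two printed numbers agree.

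A reader might go further in several directions that the document does not support:

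- *That the trial is underpowered.* For .70 on a continuous outcome, the mismatch runs the other way.
- *That the requirement should be cut to 68.* Nothing shows that .70 is the correct figure, and the primary outcomes are binary, so a total for a difference in means does not size them.
- *That .70 is a misprint for f² = .07.* With one predictor that gives 115, not 121. Reaching 121 takes f² of about .066, which is simply solved back from 121.

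**Conclusion.** The point holds in conditional form. With two-sided alpha .05, power .80, 1:1 allocation and .70 read as a standardised mean difference, the stated effect and the stated total do not belong together: .70 needs about 68, and 121 corresponds to about 0.51. The label medium sits better with 0.51, which hints that .70 is the figure at fault, but the article cannot settle that.

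Severity is moderate. The recruitment target and the analyses are unaffected, and an effect in SD units does not govern how the binary primary outcomes are read. What is lost is a clear statement of the effect on the continuous scales for which the trial was sized.

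**What to change.** Go back to the original calculation, then restate the effect size and the total so that they agree. Name the effect-size metric, the test, its sidedness and any further input used, such as a correlation or a number of predictors. If 121 is kept under a two-group comparison of means, replace .70 with a detectable standardised difference of about 0.51 (two-sided .05, power .80). If the original calculation rested on another model, state that model and its inputs so that 121 can be reproduced.

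The cost is one sentence and a look at the original calculation. Nothing in the conduct of the trial changes.

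### The recruitment target of 146 leaves about 115 participants after the plan's own 21% loss, not the 121 it says it needs; the consistent target is 154

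*Protocol article*

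**What the plan says.** The Power analysis section of the protocol article (under Data analysis) makes two linked statements:

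- For a power of .80 at the .05 level, "an overall sample size of 121 is required".
- On the basis of a previous study at the same service, the plan expects that "approximately 21% will be lost to follow up hence the target of the current study will be a sample of 146".

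The target is presented as following directly from the required number and the expected loss. The section gives no other allowance, rounding rule or working.

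**The concern.** Participants lost to follow-up are a share of those recruited. The target N must therefore satisfy N × (1 − 0.21) ≥ 121. The stated 146 does not meet this condition. It is the figure obtained by adding 21% of 121 to 121, which is a common slip and always gives too small a target.

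What is at stake is the sample-size justification itself. The plan names 121 as the number required for a power of .80, then sets a target that, at its own expected loss rate, falls short of 121. A reader would take .80 as the power after attrition, and the printed figures do not support that. The Study design section says that enrolment is still open, so the figure can still be corrected before the trial ends.

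**Working it through.** **Inputs, all from the Power analysis section**

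- Number required after losses: 121 in total
- Expected loss: approximately 21%
- Stated recruitment target: 146
- Alpha .05 and power .80. Sidedness is not stated; two-sided is assumed below and one-sided is also checked.

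Equal allocation is taken from the balanced blocks of four in the Randomisation section.

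**Step 1. Reproduce the stated figure**

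121 × (1 + 0.21) = 146.41, which rounds to 146. The stated target is reproduced by multiplication. The 25 participants added are 25/121 = 20.7% of the required number but only 25/146 = 17.1% of the number recruited.

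**Step 2. What 146 delivers at 21% loss**

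146 × (1 − 0.21) = 146 × 0.79 = 115.3, so about 115 remain. The shortfall is 121 − 115 = 6.

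**Step 3. Loss that 146 can absorb**

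1 − 121/146 = 0.171, or 17.1%.

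**Step 4. Target that matches the stated requirement and loss**

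121 / (1 − 0.21) = 121 / 0.79 = 153.2, so 154. This is 154 − 146 = 8 more than stated. Rounding up to complete blocks of four gives 156.

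**Step 5. Does rounding or the word 'approximately' explain 146?**

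| Assumed loss | 121 / (1 − loss) | Target |
|---|---|---|
| 20% | 151.3 | 152 |
| 20.5% | 152.2 | 153 |
| 21% | 153.2 | 154 |
| 21.49% | 154.1 | 155 |

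No loss rate that could be called approximately 21% gives 146. Working per arm with division by 0.79 gives totals of 152 (60 per arm), 154 (60.5 per arm) or 156 (61 per arm), and none of these is 146 either.

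**Step 6. Consequence for power**

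Take the plan at its word that 121 gives a power of .80, two-sided. In the normal approximation the standardised effect at N = 121 is then 1.960 + 0.842 = 2.802 standard errors. This scales with the square root of N:

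- At N = 115: 2.802 × √(115/121) = 2.802 × 0.975 = 2.731
- Power = Φ(2.731 − 1.960) = Φ(0.771) = 0.78

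At the unrounded 115.3 the result is 78.1% two-sided and 78.3% one-sided. Only the ratio 115/121 enters, so no effect size has to be assumed. If the calculation is framed as a two-group comparison of means, the implied standardised difference is about 0.51.

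**The case against.** The arithmetic is hard to dispute. The objections concern how much it matters.

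1. **The effect is slight.** Six participants and about two points of power change no endpoint, analysis or decision rule. This stands, and it is why a one-sentence correction is enough.

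2. **The .78 is conditional.** It assumes that 121 gives exactly .80. The section also cites an effect of about .70. Read as a standardised mean difference, .70 would need only about 66 participants in total (two-sided), and 115 would give about 96% power. This is a fair caution: .78 should be printed only with its condition. It does not remove the inconsistency, because the condition is the plan's own premise. The mismatch between 121 and .70 is a separate matter. If 121 is revised, the allowance for loss must still be made by dividing by 0.79.

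3. **Not everyone lost is unusable.** The linear mixed models for LSAS, BDI and BAI can use a participant who has baseline and post-intervention data but no final follow-up. Entry to the residential programme and three-month retention, the primary hypotheses, are binary outcomes. The article does not say whether they depend on completing the follow-up interview. This also stands. The 115 is best read as a count of participants with follow-up, and the shortfall should not be read as a demonstrated loss of power for the primary hypotheses. But the plan itself chose to inflate for loss, and it did so by too little.

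4. **Multiplication is inferred.** No working is shown, so the cause is a deduction from a numerical match. The shortfall does not depend on it: 79% of 146 is about 115 however 146 was reached.

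**Conclusion.** The point holds. The required number, the expected loss and the target contradict one another, and nothing elsewhere in the article reconciles them. At 21% loss the stated target leaves about 115 participants, 6 short of 121. It reaches 121 only if loss stays at or below 17.1%. The target consistent with the plan's own inputs is 154.

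The consequence is small: a power of about .78 instead of .80. This rests on taking 121 as giving exactly .80 and on counting everyone lost as contributing nothing, which is a worst case for the mixed models. The size of the shortfall in participants needs only the three printed figures.

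**What to change.** Correct the last sentence of the Power analysis section in one of two ways.

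- **Keep 146 and restate what it gives.** For example: with 146 recruited and 21% lost, about 115 participants are expected to have follow-up; if 121 gives a power of .80, 115 gives about .78; retaining 121 requires loss of no more than 17%.
- **Change the target to 154**, from 121 / 0.79 (156 if complete blocks of four are wanted).

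The first option costs one sentence and a slightly less favourable stated power, with no extra recruitment. The second costs 8 more participants (10 with complete blocks). Either makes the figures agree. If the basis for 121 is revisited, the target should be recalculated in the same way, by dividing the new number by 0.79.
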